### Drug composition

Each vial contains 100 mg of anakinra in 1 ml (100 mg/ml). Anakinra is a human interleukin – 1 receptor antagonist (r -metHuIL -1ra) produced by recombinant DNA technology in an E coli expression system.

### Placebo composition

Each vial consists of sodium citrate, sodium chloride, disodium edentate, polysorbate 80, sodium hydroxide and water for injection.

### Screening and enrolment

Participating centres and investigators have extensive experience of clinical trials and admit large numbers of patients with acute coronary syndromes. It is expected that screening for eligible patients will occur on a daily basis and potentially eligible patients will be approached for consent to participate. Screening for patients should occur routinely in ward areas that admit ACS patients. Centres are encouraged to screen and enrol at the weekends and out of hours depending on local resources. Each centre is requested to randomise and follow-up an average of 62 patients (30 per annum or 2–3 patients per month) over a 2 year period.

### Screening procedure

A member of the research team will screen patients for eligibility as soon as possible after presentation. If patients meet the eligibility criteria they will be given the patient information sheet to consider. Patients will be given as much time as they require to consider taking part but due to the acute nature of this condition, patients will be recruited as soon as possible after the positive troponin is confirmed. A TIMI (Thrombolysis in Myocardial Infarction) and GRACE risk score will be determined for each patient at baseline [1,37].

### Informed consent

"Informed consent" requires individual discussion with the patient about the nature of the procedures to be conducted in a language that is easy to comprehend. The patient should fully understand that he/she might be allocated to either the IL-1ra or the placebo group and the potential adverse effects of participation. The patient should also understand that his/her refusal to participate in the study will not affect the quality of subsequent medical care and if they do consent to participate they may withdraw at any point without affecting their care.

Before any trial-related procedures may be performed, informed consent must be obtained from the patient by the investigator by means of a signed declaration. The investigator must sign in the CRF to confirm that informed consent was obtained and store the original of the signed declaration of consent in the patient's notes. A copy should be given to the patient and a copy filed in the CRF.

### Randomisation

Randomisation will be performed using a 24-hour voice interactive system set up the trial co-ordinating centre (Clinical Trials and Evaluation Unit (CTEU) of the Royal Brompton Hospital, London). Centres will be asked for a few simple details about the patient including initials, date of birth and eligibility criteria. The caller will be given a randomisation number, corresponding to blinded study treatment, and a fax or e mail will be sent to the centre confirming this. Randomisation will be stratified by centre and by whether glycoprotein IIb/IIIa antagonists are being used or planned. Patients entered into the study in this way will be considered as part of the intention to treat cohort irrespective of whether they actually receive treatment or not, or if they subsequently with draw from the study.

### Study related investigations and follow-up

Patients will have blood taken every day for seven days for hsCRP (baseline and days 1–7, 14 and 30), Troponin (baseline and days 1–7 and 14), full blood count (baseline, days 7 and 14), creatinine, electrolytes, liver function tests (baseline, days 1–7 and 14), Interleukin-6 and von Willebrand factor (baseline, days 1–3,14,30). Blood will be taken prior to administration of either IL-1ra or placebo. A summary of samples and study related procedures to be undertaken is shown in Table 1. If the patient is discharged before the seventh day, they will be required to attend clinic to have the remaining blood samples taken.

**Table 1 T1:** Study procedures

Procedure	Baseline	Days 1 – 7	Days 8–13	Day 14	Day 30 (end of study)
Clinical evaluation	√	√		√	√
Informed consent	√				
Randomisation	√				
ECG	√	√		√	
Study drug given		√	√	√	
Full blood count	√	√		√	
Creatinine, electrolytes, eGFR	√	√		√	
Troponin	√	√		√	
hsCRP	√	√		√	√
Liver function tests	√			√	
IL-6, vWF	√	√		√	√
Post discharge follow up visit				√	√
Samples for DNA & RNA	√				√
Cardiac magnetic resonance scan (1)		√			√
ST segment monitoring (2)		√			
Forearm endothelial study (3)		√		√	

### Participant follow up

All patients will be followed up for MACE at 30 days (at clinic), three months and one year by telephone call with the Research Nurse. Patients will also be followed up for up to five years by the ONS.

### Collection of blood for DNA/RNA

Common genetic variations in the IL-1β gene have been shown to influence IL-1 β production and been implicated in the causation of premature coronary artery disease. IL-1β effects are mediated via the IL-1 receptor that is antagonised by IL-1ra. As with other receptors, stimulation may result in down-regulation and inhibition in up-regulation. We aim to demonstrate this by measurement of IL-1r mRNA expression. Genomic DNA and mRNA samples will be collected, stored and studied. These will be used to study the genetic substrate of observed differences in inflammatory markers and also effects of IL-1ra treatment – with initial experimental questions being as outlined here. Two additional blood samples will be taken at base-line and follow up at day 30 (1) 6 ml blood in EDTA tube for DNA extraction using the 'Versagene' DNA purification system (2) 5 ml blood in 'PAXgene' vacuum tube.

### Sub-studies

There are three sub studies proposed for the study (please see appendix 1.2. for protocols) including:

1. Cardiac Magnetic Resonance (CMR) – Leeds Patients only

2. ST-Holter segment analysis – Sheffield patients only

3. Forearm Endothelial Cell response – Edinburgh patients only

### Outcome measures

#### Primary outcome measure (comparison of treatment group with control)

Area under the curve of serum high sensitivity CRP over the first 7 days

#### Secondary outcome measures (comparison between treatment and control of)

1. Mean hsCRP at 7, 14 and 30 days

2. Area under the curve of Troponin-I

3. vWF and IL-6

4. ST segment depression on Holter monitor

5. Myocardial injury as determined by Gadolinium enhanced CMR scan

6. Forearm endothelial cell response

7. Incidence of major adverse cardiovascular events (MACE) at 30-days, three months and at one year.

8. Flagging with Office of National Statistics (ONS) for up to 5 years.

### Statistics

#### Sample size

To provide the study with an 80% power to detect a relative reduction of one-third (the reduction seen in IL-1ra treatment of rheumatoid arthritis at this dose (data on file [Amgen]) between the treatment and the placebo groups at a 5% level of significance will require approximately 80 patients in each group (total 160). This is based upon the log-transformed value of the area under the curve and a standardised difference (difference/standard deviation [D]) of approximately 0.45. The standardised difference had been used since it is very difficult to estimate what the values of the log-transformed AUC will be. A change of 0.45 on the standardised normal will correspond to a one-third change in the primary outcome, regardless of the scale of the measurement, assuming the outcome measure is normally distributed. As the sample size is sufficiently powered to detect a change equivalent to one-third on the standard normal, it will also be sufficient to detect the same level of change on the primary outcome measure. It is anticipated that follow-up will be near complete in this study. However, allowing for data loss, for whatever reason, of 10% in each arm we have increased the required sample size to approximately 180 patients (60/centre). Furthermore, the sample size needs to be adjusted for the 2 interim analyses that will be conducted during the trial. Using the method of O'Brien and Flemming (1979) gives an increased sample size of 184 patients.).

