### Interleukin 1 receptor antagonist (IL-1ra)

There are two agonistic cytokines (IL-1α and IL-1β) that signal via the Type 1 IL-1 receptor (IL-1R1) and a specific Interleukin-1 receptor antagonist (IL-1ra), (the only known naturally occurring cytokine antagonist) that inhibits IL-1 actions by binding to the IL-1R1, blocking the receptor and preventing IL-1 from binding thereby preventing receptor signalling [7].

IL-1ra is available for the treatment of a number of inflammatory conditions as a recombinant, non-glycosylated, N-terminal methionine added protein (Kineret/Anakinra, Amgen). Although less successful than anti-TNF therapies in rheumatoid arthritis (RA), there appears to be considerable benefit in the management of Juvenile arthritis (Still's disease), and it is the treatment of choice in the rare autoinflammatory illnesses typified by Muckle-Wells syndrome. From all of the indications in which IL-1ra has been used it has emerged that IL-1ra is a very safe form of treatment and appears to be devoid of the side-effect of re-activation of infectious illness seen with anti-TNF therapies. The only problems encountered are mild, reversible injection site reactions and neutropaenia in <1% of patients after a month or more of treatment.

Dosing with IL-1ra is simple. A single, daily, subcutaneous 100 mg injection of IL-1ra is the standard dose of IL-1ra for all individuals with normal renal function. In RA this causes a 35% reduction in CRP after approximately 1 week of treatment. Higher doses do not achieve any greater reduction in CRP of relief of RA symptoms. Single daily dosing schedules are used in the sucessful treatment of Juvenile arthritis and Muckle-Wells. The half-life of IL-1ra is 4–6 hours with maximum absorption from an s.c. injection at 3–7 hours. (Data on file supplied by Amgen).

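### The 80% power is stated for a one-third fall in the 7-day CRP AUC, but the effect cited to justify it is a fall in CRP level after about a week, so the power does not follow from that effect

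*Protocol article*

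**What the plan says.** All references are to the Protocol article.

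- **Target effect (Sample size).** The trial is to have "80% power to detect a relative reduction of one-third", on log-transformed AUC, with a "standardised difference (difference/standard deviation [D]) of approximately 0.45". The source given is "the reduction seen in IL-1ra treatment of rheumatoid arthritis at this dose". No SD for log AUC is stated. The section says its values are hard to anticipate and equates 0.45 SD with a one-third change.
- **What that effect is (Background, Interleukin 1 receptor antagonist).** "In RA this causes a 35% reduction in CRP after approximately 1 week of treatment".
- **Endpoint (Primary outcome measure).** "Area under the curve of serum high sensitivity CRP over the first 7 days".
- **Sampling and dosing.** "Blood will be taken prior to administration of either IL-1ra or placebo" (Study related investigations and follow-up). The Study treatment section likewise places each injection directly after sampling. Table 1 ticks study drug for Days 1–7, 8–13 and 14, and not at baseline. That is 14 doses, matching the 14-day course.
- **Minimum data (Primary analysis).** Patients with four or more follow-up readings enter the analysis. The final significance threshold is 0.045.

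**The concern.** The cited figure describes how far CRP has fallen once about a week of treatment has been given. The endpoint adds up CRP over that week, including whatever time the drug needs to act. These are different quantities, and the Sample size section moves from one to the other without a conversion.

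On Table 1's schedule the Day 1 sample is untreated and the Day 7 sample follows six doses. If baseline is a separate earlier sample and is part of the AUC, it adds a further stretch that treatment cannot affect. The untreated Day 1 reading also appears to count towards the four follow-up readings required for the primary analysis.

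This is a proof-of-concept trial. If the drug performs in NSTEMI as the protocol says it does in rheumatoid arthritis, the chance of a significant primary result may be well below the advertised 80%.

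**Working it through.** **1. Reproduce the plan's figure.** Inputs: d = 0.45, 5% level (taken as two-sided; a one-sided test would need 62 per arm and does not match), 80% power.

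n per arm = 2 × (1.960 + 0.842)² / 0.45² = 77.5, so 78. The plan says about 80. Power at 80 per arm is 81%. The arithmetic is sound for d = 0.45.

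**2. Implied SD.** On the log scale a one-third reduction is −ln(2/3) = 0.405. Equating it with 0.45 SD gives SD = 0.405 / 0.45 = 0.90.

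**3. Direction.** The AUC reduction is a weighted average of the reductions at each reading, with weights set by the control curve. If no reading exceeds reduction r and at least one is untreated (reduction 0), the average is below r for any control curve.

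**4. Size (illustrative).** Evaluable patients: 184 × 0.90 / 2 = 82.8, about 83 per arm. Alpha is 0.045. d = −ln(1 − AUC reduction) / 0.901. Power is from the two-sided noncentral t with noncentrality d × √(83/2). The AUC is by trapezoid on daily readings, with the first dose just after the Day 1 sample. A full one-third AUC reduction gives 81%.

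For a flat control curve and an immediate effect r (full by the next reading), the AUC reduction is r × 5.5/6 from Day 1 to Day 7. It is r × 5.5/7 if a full untreated day from baseline is added.

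| Flat control curve | AUC reduction, from first dose | d | Power | AUC reduction, plus untreated day | d | Power |
|---|---|---|---|---|---|---|
| Immediate 35% | 32.1% | 0.429 | 77% | 27.5% | 0.357 | 61% |
| Immediate one-third | 30.6% | 0.405 | 72% | 26.2% | 0.337 | 56% |
| One-third, half-time 1 day | 25.1% | 0.321 | 52% | 21.5% | 0.269 | 39% |
| One-third, linear over 3 days | 25.0% | 0.319 | 52% | 21.4% | 0.268 | 39% |
| One-third reached linearly at Day 7 | 16.7% | 0.202 | 24% | 14.3% | 0.171 | 18% |

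**5. Other control curves.** Two further assumed shapes were run for baseline to Day 7: a Day 2 peak (5, 10, 20, 17, 13, 10, 8, 6) and a Day 1 peak (10, 20, 17, 13, 10, 8, 6, 5). Over all three curves and both values of r:

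- immediate effect, from first dose: 64–79%;
- immediate effect, with a full untreated day: 45–69%;
- gradual onset, from a 1-day half-time to a linear build-up over 7 days, either AUC window: 9–57%.

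**6. What could restore 80%.**

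- With an immediate 35% effect, the AUC taken from the first dose and all 184 evaluable (92 per arm), power is 81% on the flat curve.
- Power depends strongly on the SD. For a 25% AUC reduction it is 52% at SD 0.90, 73% at 0.70 and 86% at 0.60. The linear ramp to Day 7 (16.7%) reaches 80% only if the SD is about 0.41 or less.

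**The case against.** The strongest reply is that the rheumatoid arthritis statement gives a time by which the fall was seen, not an onset curve. It does not exclude an earlier plateau, and the same section reports maximum absorption within hours. Rheumatoid arthritis is chronic, whereas in ACS the CRP rise is newly induced. Nothing in the protocol says that blocking a fresh rise is capped at 35%. One-third may be meant as a borrowed benchmark. This stands: it is why the conclusion is conditional on no day exceeding the cited figure. A reader might infer that the AUC reduction must be smaller than one-third, or that the trial lacks 80% power. The documents support neither as a flat statement.

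The timing is also less fixed than Table 1 suggests. The text speaks of blood daily for seven days, yet baseline plus Days 1–7 makes eight readings, so baseline and Day 1 could share a date. Table 1 and the text also disagree on liver function tests, so its ticks are not beyond doubt. The gap from baseline to the first dose is not given and may be a few hours. Whether the AUC includes that segment is not stated, and a SAP may settle it. This weakens the figures that include a full untreated day. It does not remove the point. Even if the first dose directly followed the baseline sample, one untreated reading would remain, and an immediate one-third effect on a flat curve would give 1/3 × 6.5/7 = 31.0%, close to the first-dose figure of 30.6%.

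Two further inferences should be resisted. The Background's 24–48 hour CRP peak has no stated clock origin and concerns patients treated with PCI, so it cannot show that the peak precedes dosing. And a null primary result would not stand alone: mean hsCRP at 7, 14 and 30 days and IL-6 are secondary outcomes and would help show a one-week level effect.

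**Conclusion.** The point holds in conditional form. The sample size is correct for a 0.45 SD (one-third) reduction in the AUC, but the effect cited in support is a level reached after about a week. If the drug does no better than that on any day, the AUC reduction is smaller and the stated 80% does not follow.

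The direction needs only the protocol's own text and Table 1. The size is illustrative. It rests on an SD of 0.90 back-solved from the plan, 83 per arm, alpha 0.045, and assumed onset profiles, control curves and AUC window. On those terms an immediate effect falls modestly short and a gradual one substantially short. The most favourable reading (immediate 35%, no untreated segment beyond the Day 1 sample, everyone evaluable) reaches about 80%, as would a smaller SD, for which the protocol gives no basis. This is a fault in the justification and in the anchoring of the endpoint, not proof that the trial is underpowered.

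**What to change.** 1. **Sample size wording.** Say that the 80% applies to a one-third (0.45 SD) reduction in the 7-day AUC itself, and stop presenting that as the rheumatoid arthritis effect. Add the AUC reduction expected under a stated onset and log-AUC SD, with the resulting power.
2. **AUC window.** Define the AUC as running from the last pre-dose sample to Day 7, and make the text and Table 1 agree on where baseline and Day 1 fall relative to the first dose.
3. **Minimum readings.** Count only readings taken after the first dose towards the four required for the primary analysis.

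No extra patients or samples are needed. The cost is that the stated power for the cited effect becomes less favourable. Item 2 does not by itself restore 80%: at the implied SD of 0.90 and 83 per arm, a one-third effect counted from the first dose gives 72% on the flat curve even with immediate onset.

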#### Interim analyses

A limited number of interim analyses will be performed by the trial statistician as specified by the Data Monitoring Committee (DMC). The accumulating results will not be available to the trialists or other principal investigators. The final, definitive analysis of the trial data will be conducted 25 months after the date of commencement of the trial. The interim analysis will test for efficacy, safety and futility. The method of O'Brien and Fleming suggests that stopping for efficacy will only occur if the first interim analysis shows a treatment effect equivalent to p < 0.0005 or if the second interim analysis shows a treatment effect equivalent to p < 0.014.

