#### Data monitoring committee (DMC)

The main role of the DMC is to consider the data from any interim analyses and specifically to assess any safety issues (such as unexpected serious adverse events) that occur and report back to the TSC. The DMC membership is listed in Table 3. All members of the DMC are independent of the trial. The DMC will meet prior to the start of the trial and then one and two thirds of the way through the Trial or as required thereafter. The DMC will be expected to develop, in agreement with the investigators, a charter outlining their responsibilities and operational details.

**Table 3 T3:** Data monitoring committee membership

Name	Trial Role	Title	Affiliation
[name]	Chair	Professor of Cardiology	Nottingham
[name]	Statistician	Managing Director of Nottingham Clinical Research Group	Nottingham
[name]	Cardiology advisor	Consultant Cardiologist	Sheffield

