#### Proposed study timetable

March 2006 – Grant awarded by MRC

Jan 2007 – Recruitment starts

Dec 2009 – Recruitment completed

Jan 2010 – Last patient completes 30 day follow up

2010 – Publication of data

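### The final analysis is dated 25 months after commencement, but the timetable recruits for 36 months; taken literally, the primary test would have about 65% power instead of 80%

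*Protocol article*

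**What the plan says.** All of the text is in the protocol article, in four places.

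- **Interim analyses** sets the date: "The final, definitive analysis of the trial data will be conducted 25 months after the date of commencement of the trial". Commencement is not defined.
- **Proposed study timetable** gives "Jan 2007 – Recruitment starts", "Dec 2009 – Recruitment completed" and "Jan 2010 – Last patient completes 30 day follow up", followed by publication in 2010.
- **Screening and enrolment** asks each centre to "randomise and follow-up an average of 62 patients (30 per annum or 2–3 patients per month) over a 2 year period".
- **Secondary outcome measures** lists "Incidence of major adverse cardiovascular events (MACE) at 30-days, three months and at one year". Participant follow up schedules those contacts for all patients.

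The figures that govern the primary test are in the Statistics section. They are a standardised difference of about 0.45, 80% power, 10% data loss, 184 patients after adjustment for two interim analyses (186 in the abstract), and a final threshold of p < 0.045.

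**The concern.** The date of the one confirmatory analysis and the date on which recruitment ends cannot both be followed. Month 25 from January 2007 falls around the end of January 2009, some eleven months before the timetable closes recruitment. The stated power depends on the full sample. A team that kept to the written date would test the primary outcome with nearly a third of the patients not yet randomised. A team that waited would depart from the written date on its own judgement during the trial, which a pre-specified analysis time is meant to prevent.

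One-year MACE is a listed secondary outcome. No analysis dated at month 25 can contain it in full, and the article does not say outright that it will be analysed later.

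**Working it through.** **Assumptions not in the document:** commencement is the start of recruitment (January 2007), accrual is uniform, and the test is two-sided.

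**1. Where the 25 months comes from.**
- Two-year recruitment: 24 + 1 month for the 30-day visit = 25. This reproduces the stated date.
- Timetable: January 2007 to December 2009 inclusive is 36 months, and 36 + 1 = 37. This does not.
- The accrual rate also points to two years. 62 patients per centre over 24 months is 2.6 per month, inside the stated 2–3. Over 36 months it is 1.7 per month, below that range.

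**2. The plan's own sample size.**
- For D = 0.45, 80% power and 5% two-sided, the normal formula gives 78 per arm, against the plan's approximate 80.
- 160 / 0.90 = 178, against approximately 180.
- An assumed O'Brien-Fleming inflation of about 1.017 for three looks gives 180 × 1.017 = 183, against 184.

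The sample size is sound at full information.

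**3. Patients available at month 25 of a 36-month recruitment (N = 186).**
- Randomised: 25/36 = 69.4%, or 129. Not yet randomised: 57.
- With 7-day data: 186/36 × (25 − 0.23) = 128 (69%).
- With 30-day data: 24/36 = 66.7%, or 124.

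Using 184 instead of 186 changes these counts by one or two patients.

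**4. Power of the primary test** (two-sample t, D = 0.45, two-sided alpha 0.045).

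| Situation | Evaluable per arm | Power |
|---|---|---|
| Month 25, 10% loss | 128 × 0.9 / 2 = 57.6 | 65% |
| Month 25, no loss | 128 / 2 = 64 | 70% |
| All 186, 10% loss | 186 × 0.9 / 2 = 83.7 | 81% |

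**5. Type I error** (simulation, 4 million runs, stated thresholds 0.0005, 0.014 and 0.045).
- Looks at 1/3, 2/3 and full information: 5.0%.
- Looks at 1/3 and 2/3, then a single final test at 0.69 of the information: 4.5%.

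**6. One-year MACE complete at month 25.**
- 36-month recruitment: (25 − 12)/36 = 36%, or 67 of 186.
- 24-month recruitment: (25 − 12)/24 = 54%, or 101 of 186.

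**7. Sensitivity to the meaning of commencement.** If it meant the grant award in March 2006, month 25 would fall about April 2008. That is 15 to 16 months into recruitment, with 42–44% of patients randomised.

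**The case against.** The strongest reply is that the 25 months is a leftover date. It equals two years of recruitment plus the 30-day visit, and on that schedule every patient has primary and 30-day data at month 25. The sample size section asks for 184 patients, and the timetable puts publication after the last 30-day visit. Nothing suggests an intention to stop at about 128. This stands as the likely cause. It does not remove the contradiction, because the timetable still conflicts with the other two sections.

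A reader might draw three stronger conclusions, which the document does not support.

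- **That the type I error is inflated.** That would need a test at month 25, continued recruitment and then a second final test. The plan describes one final analysis, and a single early one stays below 5% (step 5).
- **That the second interim would fall a month before the final analysis.** The DMC meets "one and two thirds of the way through the Trial", but the article does not say whether that is measured in calendar time or in patients. It leaves the interim analyses to the DMC, with a charter to follow.
- **That one-year MACE would be reported on a minority of patients.** This is true only under 36-month recruitment. The same outcome list includes national statistics flagging for up to five years, and the publication policy mentions a final follow-up paper. Both suggest later reporting, so the gap is that the separate analysis is not stated.

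**Conclusion.** The point holds as an unreconciled date that governs the primary test. The 25-month analysis fits a two-year recruitment and contradicts the 36-month timetable. If it were followed literally on that timetable, power would fall from the stated 80% to about 65% with the planned 10% loss, or 70% with none. The loss is one of power only. These figures rest on uniform accrual and on commencement in January 2007, and an earlier commencement would make them worse. If recruitment in fact takes 24 months, the primary analysis is unaffected. One-year MACE is incomplete at month 25 in either case (36% or 54% of patients complete). The document does not show that anyone planned to analyse two-thirds of the trial.

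**What to change.** 1. In Interim analyses, replace the 25-month date with a data trigger: the final primary analysis runs once all 184–186 randomised patients have completed Day 30 and the hsCRP data are locked.
2. State that one-year MACE is analysed separately after the last 12-month contact, which is about December 2010 on the published timetable.
3. Give the same recruitment period in Screening and enrolment, Interim analyses and Proposed study timetable.

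The cost is a wording amendment. The one downside is that the primary result is read later than month 25 if recruitment takes 36 months, and the timetable already assumes that.
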